### Recruitment

Based on a power calculation (see Section 2.7.), a total of 317 patients will be required for the data analysis. On the basis of data from the Danish National Alcohol Treatment Register (48) and prior studies conducted at this clinic (49–52) and prior studies of AACTP (32, 36, 42), it seems feasible that at least 317 eligible patients (see Section 2.4.) can be recruited from January 2021 to July 2022.

After completing detoxification and prior to starting primary treatment, each patient will be briefly informed about the project and asked whether he or she is willing to meet with a research assistant who will provide further information about the study. If the patient agrees, the research assistant will provide the patient with oral and written information about the details of the study. After informed consent has been provided, a baseline interview will be conducted, and each patient meeting the eligibility criteria will be randomized. To minimize the risk of bias and to overcome potential group imbalances, the current study will utilize an urn technique that will randomize the patients to one of the three treatment groups.

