### Experimental and Control Groups

The 317 patients (see power analysis below) fulfilling the eligibility criteria will be randomized to one of the three groups: Group A: AACTP delivered *via* a smartphone application + treatment as usual (TAU; *n* = 106), Group B: ACTP sham training delivered *via* a smartphone application + TAU (*n* = 106), or Group C: TAU only (*n* = 106). Patients in Group A will receive seven sessions of AACTP (one session per week for 7 weeks). Patients in Group B will receive seven sessions of sham training (one session per week for 7 weeks). Patients in Group C will receive only the primary treatment for AUD. Patients in the AACTP and sham control groups will start the primary treatment within the 1st month of their admission, so that the add-on treatment will not extend beyond the 3-month treatment period.

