A power analysis (79, 80) was conducted using G^*^Power for a repeated-measures MANOVA with α = 0.05; effect size (ES) of *f* =0.20; power = 0.90; groups *k* = 3; and time-points measurements = 4. It showed that 88 participants will be required for the final analyses in each of the four cells (total *N* = 264). Prior evaluations identified *f* s of 0.30 (AB) and 0.37 (weekly mean drinking) and an *f* of 0.42 (situational confidence to resist drinking) on outcome measures for sub-clinical excessive drinkers (36). Further, in a study that used the intervention as an add-on treatment for clinical participants with a substance-use disorders other than AUD, effect sizes of *f* s = 0.33 (drug-specific AB), 0.34 (number of relapses), 0.32 (temptation to use) and 0.37 (self-confidence to resist temptation) were identified (42). Also, an unpublished study conducted with detoxified drug-abusers found *f* s of 0.39 (drug-specific AB), 0.18 (number of relapses), and 0.35 (temptation to use) (81). A second power analysis for a MANOVA with special effects and interactions was conducted to test the dosage-effect across groups (α = 0.05; EF *f*
^2^(*v*) = 0.06; power = 0.90; *k* = 3; predictors = 3; and response variables = 8), which yielded an *N* of 220. Attrition in similar studies has usually ranged from 10 to 15% (41, 42). Assuming a somewhat higher attrition rate (20%), which is not unlikely (82, 83), indicates that 317 (264 + [264·0.20]) participants should be tested at baseline for an analysis using listwise deletion of missing cases, although a multiple imputation (MI) analysis will also be conducted to verify that results converge across missing data assumptions. The projected sample size is sufficient for the planned data analyses, including mediational analyses based on Fitz and MacKinnon's guidelines (84).

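### The 20% attrition allowance is added to the completers instead of divided out, so 317 enrolled leaves about 254 complete cases, not the 264 the plan requires

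*Protocol article*

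**What the plan says.** The power calculation in the Statistical Analysis section is for a "repeated-measures MANOVA with α = 0.05", with an "effect size (ES) of *f* =0.20" and "power = 0.90; groups *k* = 3; and time-points measurements = 4". Its result is that "88 participants will be required for the final analyses in each of the four cells", with a total of 264.

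The section reports 10 to 15% attrition in similar studies, adopts 20% as a more cautious figure, and concludes that this "indicates that 317 (264 + [264·0.20]) participants should be tested at baseline". It says this baseline number is for an analysis with listwise deletion. Multiple imputation is to be run as well, to see whether the results agree.

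The target appears in two other places besides the abstract:

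- Recruitment: "a total of 317 patients will be required for the data analysis".
- Experimental and Control Groups: "The 317 patients (see power analysis below) fulfilling the eligibility criteria will be randomized to one of the three groups", followed by n = 106 for each group.

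**The concern.** An attrition rate is a fraction of the people enrolled. To finish with n complete cases when a fraction d is lost, one enrols n/(1 − d). The plan enrols n(1 + d), which is always too few. The 53 extra patients are 20% of 264 but only 16.7% of 317.

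At stake is the trial's main enrolment target. If attrition runs exactly as assumed, the complete-case analysis misses the size the plan calls necessary, yet the same section describes the projected sample as sufficient.

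The surrounding figures do not help the reader settle what was meant. They give different answers on how many groups the 88 applies to, how many patients are randomised, and whether 317 is an enrolment or an analysis number.

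**Working it through.** **Inputs (all from the Statistical Analysis section unless noted)**

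- Required complete cases: 88 per group, 264 in total.
- Assumed attrition: d = 0.20; similar studies: 0.10 to 0.15.
- Group sizes: 106 each (Experimental and Control Groups).
- Power inputs: α = 0.05, f = 0.20, power 0.90, k = 3 groups, m = 4 time points.

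**1. Reproducing the plan's figure**

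264 × (1 + 0.20) = 316.8, rounded to 317. This is the plan's own printed formula, so the source of the number is not in doubt.

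**2. What 317 delivers at 20%**

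317 × (1 − 0.20) = 253.6, which is 10 to 11 below 264. Per group, 106 × 0.80 = 84.8 against 88.

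**3. The number that would deliver 264**

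264/(1 − 0.20) = 330, or 88/0.80 = 110 per group. That is 13 more than 317, and 12 more than 3 × 106 = 318.

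**4. The attrition 317 can absorb**

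1 − 264/317 = 16.7%. For 318 it is 1 − 264/318 = 17.0%.

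| Attrition | Completers from 317 | Enrolment needed for 264 |
|---|---|---|
| 10% | 285.3 | 293.3 |
| 15% | 269.5 | 310.6 |
| 16.7% | 264 | 317 |
| 20% | 253.6 | 330 |

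**5. Linked figures**

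- 88 × 3 = 264, but 88 × 4 = 352. Only three groups agrees with the stated total, with k = 3 and with the design.
- 3 × 106 = 318, not 317 (317/3 = 105.67).
- Recruitment gives 317 as the number for analysis; Statistical Analysis gives 264 for analysis and 317 at baseline.

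**6. Effect on power**

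The plan does not name the G*Power option or the within-person correlation, so three readings were tried.

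- *264 taken as exactly 90% power, whatever the model.* Choosing f in the interaction test below so that 264 gives 0.90 yields f = 0.183; 253 completers then give 0.885.
- *Time × Group interaction, the plan's criterion for efficacy, with f = 0.20.* Pillai's trace with s = min(k − 1, m − 1) = 2, df1 = (k − 1)(m − 1) = 6, df2 = 2(N − 4) and noncentrality λ = N·s·f². At N = 264, λ = 264 × 2 × 0.04 = 21.12 and df2 = 520.
- *Between-group effect with f = 0.20 and an assumed correlation ρ = 0.75.* λ = N·f²·m/[1 + (m − 1)ρ], with 2 and N − 3 degrees of freedom.

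| Reading | N for 90% power | Power at 264 | Power at 254 | Power at 253 |
|---|---|---|---|---|
| 264 set to 90% | 264 | 0.900 | 0.886 | 0.885 |
| Interaction, f = 0.20 | 221 | 0.950 | 0.941 | 0.940 |
| Between groups, ρ = 0.75 | 261 | 0.905 | 0.893 | 0.891 |

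**The case against.** The strongest reply is that the shortfall has little practical effect. Similar studies lost 10 to 15%, and 317 covers that whole range, leaving about 269 to 285 completers. The target fails only inside the extra margin the plan added, by 3 to 4 patients per group. The cost in power is about 1.5 points on the least favourable of the readings above. On the interaction test with the stated inputs, power stays above 0.90. The side discrepancies are editorial: k = 3 and the total of 264 show that three groups was meant, 318 is rounding, and the Recruitment wording is loose but recoverable from the other sections.

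Most of this stands as a limit on the consequences. It also means that the 0.94 figure should not be stated without its assumptions, because another G*Power option puts power nearer 0.89. None of it makes the calculation right. The plan chose 20%, calls that rate not unlikely, and presents 317 as the number that protects against it.

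Multiple imputation does not rescue the figure either, since the plan ties 317 to listwise deletion and treats imputation as an additional check. Nor is this detail that an article would leave to a fuller document: the number, its derivation and its purpose are all printed, and they do not agree.

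**Conclusion.** The point holds. At the attrition the plan assumes, 317 enrolled leaves about 254 complete cases, 10 to 11 fewer than the stated requirement. The figure consistent with 264 completers and 20% loss is 330; 317 is consistent with 16.7% loss.

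The conclusion rests only on the plan's 264, its 20%, and the usual meaning of attrition as a share of those enrolled. If attrition stays at or below 16.7%, no shortfall occurs.

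The loss is modest. Power at about 253 to 254 completers lies between roughly 0.885 and 0.94 across the readings tried, depending on a model and correlation that the plan does not state. This is a wrong sample-size statement with inconsistent companion figures, and not a threat to the trial's ability to answer its question.

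**What to change.** Choose one of two statements and use it in the abstract, Recruitment, Experimental and Control Groups, and Statistical Analysis:

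1. **Keep the enrolment.** Say that 318 patients (3 × 106) will be enrolled, that about 254 completers (about 85 per group) are expected at 20% attrition, and that 264 completers are reached only if attrition is at most about 17%.
2. **Keep 264 completers at 20% attrition.** Say that 264/0.80 = 330 patients (110 per group) will be enrolled.

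In either case, replace four cells with three groups, use one enrolment total that equals the sum of the group sizes, and state in Recruitment that 264 is the number for analysis while the larger figure is the number to enrol.

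The first option costs only wording, plus a slightly less favourable stated number of completers. The second adds 12 patients to 3 × 106, or 13 to 317. Neither changes the design or the analysis.

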## Abstract

**Background:** There is consistent evidence that community and clinical samples of individuals with an alcohol use disorder (AUD) have attentional biases toward alcohol cues. The alcohol attentional control training program (AACTP) has shown promise for retraining these biases and decreasing alcohol consumption in community samples of excessive drinkers. However, there is a lack of evidence regarding the effectiveness of ACTP in clinical AUD samples. The main aim of the present study is to investigate whether primary pharmacological and psychological, evidence-based alcohol treatment can be enhanced by the addition of a gamified AACTP smartphone application for patients with an AUD.

**Design and Methods:** The study will be implemented as a randomized controlled trial. A total of 317 consecutively enrolled patients with AUD will be recruited from alcohol outpatient clinics in Denmark. Patients will be randomized to one of three groups upon initiation of primary alcohol treatment: Group A: a gamified AACTP smartphone application + treatment as usual (TAU); Group B: a gamified AACTP sham-control application + TAU; or Group C: only TAU. Treatment outcomes will be assessed at baseline, post-treatment, and at 3- and 6-month follow-ups. Repeated measures MANOVA will be used to compare the trajectories of the groups over time on alcohol attentional bias, alcohol craving, and drinking reductions. It is hypothesized that Group A will achieve better treatment outcomes than either Group B or Group C.

**Perspectives:** Because attentional bias for alcohol cues is proportional to the amount of alcohol consumed, and these biases are not addressed within current evidence-based treatment programs, this study is expected to provide new evidence regarding the effectiveness of the gamified AACTP in a clinical population. Furthermore, due to promising results found using AACTP in community samples of excessive drinkers, there is a high probability that the AACTP treatment in this study will also be effective, thereby allowing AACTP to be readily implemented in clinical settings. Finally, we expect that this study will increase the effectiveness of evidence-based AUD treatment and introduce a new, low-cost gamified treatment targeting patients with an AUD. Overall, this study is likely to have an impact at the scientific, clinical, and societal levels.

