### Statistical Analysis

The intent-to-treat principle will be followed in the analyses to evaluate the intervention. A repeated-measures MANOVA with groups as the between-participants factor and assessment time-point as the within-participants factor will be used to test the efficacy of the intervention across the assessment points. Efficacy would be indicated by a significant Time X Study Group interaction. Each of the significant interactions will be followed up with *post-hoc* tests to identify the source of the interaction. Potential demographic covariates (e.g., age, education, income) will also be considered by using MANCOVA. Further, attrition rate at each follow-up time point will be evaluated. Baseline characteristics of participants who remain in the study will be compared with those who have been lost to follow-up. A multiple imputation (MI) approach that adjusts for uncertainty arising from missing data (76, 77) will also be conducted to evaluate the main findings.

Based on MacKinnon (78) mediational procedures, a series of regression analyses will be conducted to test the hypothesized mediational relationships among the outcome variables, i.e., that reductions in *alcohol AB* and *cravings* will partially mediate improvements in the outcome measures. Several ancillary interaction effects will also be evaluated, although they are not hypothesized to be significant. They include potential interactions between the intervention received and patients' drinking history, affective states, and cognitive flexibility. Although the intervention is intended to be effective for all AUD patients, it is important to test this assumption by evaluating whether the intervention is effective for specific sub-groups of patients.

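### The main efficacy test is a listwise-deletion MANOVA with baseline as one of its outcomes, which contradicts the intent-to-treat statement and leaves multiple imputation only as a check

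*Protocol article*

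**What the plan says.** The Statistical Analysis section opens with the commitment "The intent-to-treat principle will be followed in the analyses to evaluate the intervention". It then names the model: "A repeated-measures MANOVA with groups as the between-participants factor and assessment time-point as the within-participants factor will be used". The criterion is "Efficacy would be indicated by a significant Time X Study Group interaction".

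The time factor has four levels. The power paragraph gives "power = 0.90; groups *k* = 3; and time-points measurements = 4", and the Abstract lists them: "Treatment outcomes will be assessed at baseline, post-treatment, and at 3- and 6-month follow-ups". Baseline is therefore a level of the outcome. The only covariates named are demographic examples; baseline drinking is not among them.

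On missing data, the power paragraph inflates 264 analysed patients by 20% and says that 317 "participants should be tested at baseline for an analysis using listwise deletion of missing cases". The sentence continues: "although a multiple imputation (MI) analysis will also be conducted to verify that results converge across missing data assumptions". Earlier in the section, imputation is likewise an additional step for evaluating the main findings. The section also plans to report attrition at each follow-up and to compare the baseline characteristics of retained and lost patients.

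**The concern.** An analysis restricted to patients seen at all four time-points is a completer analysis. The intent-to-treat statement and the listwise statement cannot both describe the decisive test.

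This matters because the primary outcome is weekly mean drinking, and return to drinking is a plausible reason to miss a visit. The Background reports relapse in as many as half of patients within 6 months of discharge, which is the follow-up window here. The arms also ask different things of patients: seven weekly training sessions, seven weekly sham sessions, or no app. If loss depends on drinking in different ways across arms, the completers are no longer comparable and the contrast can shift in either direction.

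The second issue is precision. Entering baseline as an outcome rather than a covariate tests differences in change. In a randomised trial that is valid, but it is less efficient than adjusting for the same baseline measurement.

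**Working it through.** **1. The plan's figures.** 264 × 1.20 = 316.8, rounded up to 317, so the baseline N reproduces.

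**2. Patients excluded.**
- From the two totals: 317 − 264 = 53, and 53/317 = 16.7%.
- From the stated 20% attrition: 317 × 0.20 = 63.4, leaving 253.6 (about 254).

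**3. Is the stated power lost?** Inputs from the power paragraph: "repeated-measures MANOVA with α = 0.05", f = 0.20, 3 groups, 4 time-points. For the interaction (Pillai), s = min(2, 3) = 2, df1 = 2 × 3 = 6, df2 = 2(N − 3 − 3 + 2), and noncentrality is N × s × f².

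| N analysed | Power |
|---|---|
| 221 | 0.90 |
| 254 | 0.94 |
| 264 | 0.95 |

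Under this calculation 264 corresponds to power 0.95 rather than the stated 0.90, which is a separate matter. With 254 completers the stated 0.90 is still met.

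**4. Cost of using baseline as an outcome.** With equal variances σ² and baseline-to-follow-up correlation rho, the per-patient variance is 2σ²(1 − rho) for a change score and σ²(1 − rho²) after baseline adjustment. The ratio is 2/(1 + rho). The document gives no correlation, so rho is assumed.

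| rho | Change / adjusted |
|---|---|
| 0.3 | 1.54 |
| 0.5 | 1.33 |
| 0.7 | 1.18 |

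**5. Cost of discarding partial data.** Assumed: two arms of 317/3, 80% completers, equal correlations of 0.3 to 0.7 between visits, baseline adjustment in both analyses.
- 6-month contrast: using incomplete patients as well lowers the variance by 0 to 3% if dropout is monotone, and by about 15% if single visits are missed.
- Average over post-baseline visits: 0 to 12%, and about 17%.

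**6. Steps 4 and 5 together.** The table gives the 6-month variance of a baseline-adjusted analysis of all available data, as a fraction of the listwise change-score variance.

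| rho | Fraction |
|---|---|
| 0.3 | 0.55 to 0.65 |
| 0.5 | 0.64 to 0.75 |
| 0.7 | 0.72 to 0.85 |

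Baseline adjustment alone gives the upper end of each range (0.65, 0.75, 0.85).

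**7. Bias of the completer contrast.** Simulated with no true effect and logistic dropout depending on post-treatment drinking. The slope is per SD of drinking; all mechanisms are assumed.

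| Dropout, arm 1 / arm 2 | Correlation between visits | Post-treatment change (SD) | 6-month change (SD) |
|---|---|---|---|
| slope 1, 20% / slope 1, 20% | equal | 0.00 | 0.00 |
| slope 1, 25% / slope 1, 15% | equal | −0.04 | 0.00 |
| slope 1, 20% / slope 0, 20% | equal | −0.09 | 0.00 |
| slope 1, 25% / slope 0, 15% | equal | −0.11 | 0.00 |
| slope 1, 25% / slope 0, 15% | autoregressive 0.7 | not tabulated | 0.05 |
| slope 1, 25% / slope −1, 15% | autoregressive 0.7 | not tabulated | 0.07 |

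A second simulation had a true effect of −0.42 SD, correlation 0.3 from baseline to follow-up and 0.7 among follow-ups, and about 20% loss per arm. With drinking-related loss in the control arm only, the listwise change estimate was −0.33; with such loss in Group A only, it was −0.50. A baseline-adjusted analysis valid under missing at random gave −0.42 both times. With the same mechanism in both arms, the two estimates were −0.41 and −0.42. Equal dropout rates therefore do not show that bias is absent.

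**The case against.** The strongest reply is that listwise deletion appears only in the sample-size sentence, that sizing for the worst case is prudent, and that imputation is mentioned twice, alongside a comparison of retained and lost patients. On this view only the wording needs tidying. Part of this stands: the plan does contain protection against selective loss. But a classical repeated-measures MANOVA needs a complete set of visits, and both mentions give imputation an additional role. Followed as written, the completer test decides efficacy.

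A reader might infer more than the documents support:

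- **That power is lost.** It is not; N was inflated for the expected exclusions.
- **That dropped patients are the main cause of lost precision.** Most of the loss comes from how baseline is used. The partial-data component is small unless single visits are missed.
- **That listwise deletion is necessarily biased unless data are missing completely at random.** With the same mechanism and rate in both arms, the simulated change contrast was unbiased.
- **That the protocol shows dropout to be drinking-related.** It reports relapse but does not link relapse to missed visits, and it cites 10 to 15% attrition in similar studies.

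It is also fair that the simulations concern two-arm contrasts, not the planned three-group, 6-df test, and that baseline as a repeated level is inefficient rather than invalid.

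**Conclusion.** The point holds in a limited form and should be corrected. The decisive test, as described, excludes about 53 to 63 of 317 randomised patients, contrary to the stated principle. Protection against selective loss is missing from the main analysis, though not from the plan as a whole.

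The possible bias, roughly 0.07 to 0.11 SD, illustrates assumed mechanisms that differ by arm. It is not a forecast or an upper limit, and it is nil when dropout works identically in all arms. The change-score penalty of 1.54 to 1.18 in variance is exact given equal variances and the assumed correlations of 0.3 to 0.7.

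Agreement between listwise deletion and standard imputation would give limited reassurance. Standard imputation assumes missing at random, so such agreement does not address dropout that depends on unobserved drinking.

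**What to change.** Name one primary analysis of all randomised patients and make the power paragraph refer to it:

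- **Primary:** a likelihood-based repeated-measures model, or the multiple imputation already planned. Outcomes are weekly mean drinking at post-treatment, 3 months and 6 months, with arm, visit and their interaction, and baseline weekly drinking as a covariate. The Recruitment section places the baseline interview before randomisation, so the covariate should be available for nearly everyone. Patients with no later assessment add almost nothing to the likelihood model; if they are to appear explicitly, use imputation.
- **Sensitivity:** keep the listwise MANOVA, labelled as a completer analysis.
- **Optional:** a delta-adjusted imputation in which missing patients are assumed to drink progressively more. This, model details such as the covariance structure, and further covariates may sit in a statistical analysis plan.

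The cost is some rewording and a little more analysis work. No new data or visits are needed. The change should be made before outcome data are seen by arm.
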